#### Data Access and Use

To access the data, scientists from IfADo, as well as external cooperation partners who plan to analyze data from the Dortmund Vital Study fill in a proposal form that includes a short description of the project and the respective hypotheses, responsible persons, cooperation partners, data usage, and analysis strategy. The requested research data will be made available in an anonymized form after consultation with the scientists responsible for the data. Responsible persons include project managers and coordinators of the Dortmund Vital Study in consultation with the IfADo Research Data Management Unit.

After primary analyses and publication of the main results, the data and the scripts used for data analyses will be made available in repositories for secondary analyses. The transfer agreement will be prepared by the coordinators of the Dortmund Vital Study in consultation with the IfADo Research Data Management Unit. Data access will be restricted and will require a structured project proposal. Access to the SQL database will be password protected. Interoperability will be guaranteed by metadata included in the SQL database and common data formats (eg, BIDS) to enhance exchange, management, and documentation. Data identifiers (digital object identifiers) will be assigned at least until the end of the projects.

#### Organization, Management, and Policies

Central organizational support for data management is provided by the Research Data Management Unit at IfADo.

The Dortmund Vital Study is funded by the institute’s budget. Thus, the study design, collection, management, analysis, interpretation of data, writing of the report, and the decision to submit the report for publication is not influenced by or biased toward any sponsor.

Permissions for the tests, questionnaires, and software used that are subject to copyright were obtained from the corresponding publishers. If no license was required, permission was granted by the authors of the corresponding questionnaire or test.

### Data Analysis

Detailed descriptions of the specific data analysis methods depending on the type of measure will be provided in subsequent publications.

Generally, for all quantitative variables, descriptive statistics, frequencies, and distributions will be calculated for all participants. Summary statistics including the mean, SD, minimum values, and maximum values will be provided for quality assurance. Qualitative variables will be categorized before performing any statistical analysis. Immunological, biochemical, medical, optometric, and audiometric data as well as coding for genetic polymorphisms are integrated in the SQL database. Data from psychometric tests in the SQL database will be verified by using an automated MATLAB script for plausibility and outliers. EEG and behavioral data from experimental tasks will be analyzed with EEGLAB [108] using scripts. The main parameters, such as individual amplitudes or latencies of transient components, time-frequency parameters, or behavioral data, such as reaction times, error rates, and SDs, will be automatically written in the SQL database.

Depending on the research topics and questions, different methods will be used for data analysis. For the cross-sectional analyses, mixed ANOVA, Analyses of Covariance (ANCOVA), 1-way ANOVA, or *t* tests will be used. Furthermore, the Pearson correlation coefficient or appropriate regression models will be used to identify predictors of the variables of interest. Moreover, the structural equation modeling approach and novel decoding techniques will be employed when appropriate.

For the longitudinal data, mixed model ANOVA including within-subject factors, such as Time Point of Measure, and between-subject factors, such as Age Group, will be employed. Interactions will be analyzed using simple ANOVA or *t* tests. Additionally, covariance analysis (ANCOVA) will be conducted to control for potential confounding factors like gender and education. It is not intended to impute missing data for ANOVA or ANCOVA. In case of a few or moderate number of missing data, the analyses will be conducted with the complete cases. In case of a larger number of missing data over the long period, advanced statistical approaches like the Generalized Estimating Equation (GEE) [109] or Mixed Effect Regression (MER) [110] will be used.

### Ethics Approval

The first run of the Dortmund Vital Study (2016-2021) was conducted with approval from the local Ethics Committee of the IfADo in 2015. Follow-up testing was approved in July 2021 by the Ethics Committee of the IfADo (approval number: A93-3).

## Results

The baseline testing was conducted between 2016 and 2021. As of August 2021, 593 participants were tested. In October 2021, the first follow-up measure was started. Some initial results from the cross-sectional part of the study were already published [83, 111-116]. Longitudinal data will be analyzed, and the first publications are estimated for 2025.

## Discussion

### Study Overview

The Dortmund Vital Study is a multidisciplinary long-term project, combining a cross-sectional and longitudinal study design. The goal is to investigate the influence of a wide range of biological and environmental factors on cognitive functions and their neurophysiological correlates as well as on the immune system and other physiological functions and structures. The combination of well-elaborated experimental paradigms reflecting basic cognitive functions, modern EEG methodology, MRI scans, lifestyle data, and the analysis of biochemical parameters will facilitate the development and evaluation of specific hypotheses on the mechanisms of healthy and pathological aging from different perspectives and disciplines. Work-related human factors (eg, type of work), work ability, and the role of work conditions (eg, stress or job satisfaction) will be of particular interest. Moreover, the Dortmund Vital Study has the potential to shed tremendous light on the complex interactions between immunological, genetic, metabolic, and brain-related parameters in healthy adults. Specifically, parameters obtained by MRI and EEG-related measures can be evaluated as a function of the PGS, metabolic products, concentration of immune cells, immune age, and infections such as Toxoplasmosis or COVID-19 that are largely unexplored. The same is true for environmental and lifestyle factors that influence brain activity and behavior. As human behavior and cognition reflects a combination of these factors, the Dortmund Vital Study has the potential to elucidate several important findings. Crucial points are the developmental aspect and the progress or decline of several functions over the lifespan. This design enables analysis of changes of inter- and intraindividual variability with increasing age and lead to conclusions, such as which factors in the past have the largest impact on the present measures or pathological outcomes like burnout, depression, mild cognitive impairment, or dementia. In conclusion, this multidomain and interdisciplinary study will help elucidate underlying mechanisms of healthy and pathological aging.

### Limitations and Future Challenges

A challenging problem in longitudinal study designs is the dropout rate, especially during long test periods like in this study. The dropout rate can be affected by unpredictable events like the present COVID-19 pandemic. A reduced number of participants during follow-up produces missing values, shrinks the entire sample size, reduces the statistical power, and may lead to a small sample size at the end of the study relative to the number of analyzed variables.

Thus, it is important to analyze the reasons for dropouts and whether the participants are missing at random or not at random (ie, due to unsystematic or systematic reasons), which may differently affect the results. For example, dropouts due to lack of interest in further participation in the study or change of residence can be treated as random. In contrast, dropouts due to illness or death could reflect a systematic reason for missing data, given that elderly participants entering the study have a much higher risk of illness or death in the long period spanning 20 years. This may lead to a disproportionate dropout in this age group compared to the younger groups. Moreover, a pandemic like COVID-19 reflects a systematic source of dropouts.

Missing data have important consequences for data analysis. Repeated measures ANOVA or MANOVA requires fully complete data sets for each repeated measure. That is, without data imputation, only a reduced (but complete) data set can be used for analysis. There are several methods to counteract this using statistical approaches. For example, the missing data can be replaced by the last measured data or by a simple or conditional mean of the variable resulting from a predicted value. However, data imputation is generally not recommended, and instead, other methods should be used to deal with missing data sets [117].

For the present design, a GEE [109] model will be used, which is robust to misspecifications of the repeated measures’ correlation structure, time irregularities, and does not require excluding participants with incomplete data sets. An alternative method would be MER [110], in which random effects can serve to describe each participant’s trend over time. MER assesses longitudinal changes of several outcomes and is even more robust to missing data than the GEE. Both models allow time-invariant predictors (eg, biological gender, genotype) and time-varying predictors (eg, age, metabolic, immunological, or cognitive parameters), and handle irregularly timed and missing data without the need for imputation [118]. An advantage of these procedures is that both can model time-varying predictions useful for understanding changes in cognitive aging.

Nevertheless, the relatively large number of participants in this study that primarily aims to analyze cognitive changes using neuropsychology, EEG, and MRI is unique and even taking dropouts into account allows answering important scientific questions. For example, when interested in age-related changes in an electrophysiological parameter, a group of approximately 40 participants would still be sufficient to track the changes across the span of 20 years. Generally, we expect the dropout rate to remain constant and to be able to analyze the data with a sufficiently large sample at least for the first follow-up measures 5 and 10 years after the beginning of the study.

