#### Hypothesis 1: Background and Mechanisms of Stress-Related Exhaustion Disorder

Burnout, a synonym for stress-related exhaustion disorder is a widespread phenomenon, but the underlying mechanisms have not yet been sufficiently explored. In addition, there is no clear distinction between burnout and depression [20,21], and there is currently limited evidence connecting burnout and cognitive functions [22,23]. However, it is known that the reward system in the orbitofrontal brain areas is altered owing to depression and subclinical depressive symptoms, which is evident in electrophysiological correlates [24]. As a result, the perception of mistakes or negative feedback is increased whereas the sensitivity to rewards is decreased [25]. The reward system is based on complex cognitive abilities, the so-called executive functions, which enable goal-directed behavior. Therefore, it is important to compare the effects of burnout and depression using the same parameters and measures and identify similarities and differences with respect to executive functions between the 2 disorders. We expect that individuals with high scores on the burnout scales will perform poorly in cognitive tasks and in tests measuring executive functions, such as working memory, task switching, decision-making, or distractibility. Additionally, we aim to explore possible differences in the resting-state electroencephalography (EEG) and functional MRI brain activity between burnout and nonburnout employees; we expect reduced alpha power and cortical hyperactivity in the former group [26] that may be the neuronal correlate of hypersensitivity to negative events. However, no effects are expected in tasks that measure basal cognitive functions such as vigilance or processing speed. Moreover, a relationship between burnout and immunological parameters [27,28] or metrics of immunological age can be assumed. For example, the concentration of hair cortisol as an index of long-term stress is expected to be positively related to the severity of burnout symptoms and reduced cognitive performance [29,30].

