## Methods

### Study Population

The participants of the Dortmund Vital Study (trial registration number: NCT05155397) represent a sample of a generally healthy population of a western society aged between 20 and 70 years. We define “healthy” in a rather broad sense and allow the inclusion of individuals who are smokers, drink alcohol, are overweight, or have a history of diseases without having severe symptoms. Moreover, we do not impose restrictions regarding education or occupation to enhance the representativity of the sample. Participants are recruited via an internet site, newspaper advertisements, reports and announcements in local print and radio media, public information events, social media, and flyers throughout the city of Dortmund, Germany. In addition, some larger companies in the region were contacted and asked to inform their employees about participating in the study. The number of subjects resulted from a biostatistical estimation (power analysis), in which the size of the expected effects and their variance were considered. The study parameters will be collected repeatedly for 4 time points, namely at the start of the study (baseline), and then 5, 10, and 15 years later (time points for measuring within-subject factors) and between 3 age groups (between-subject factor ie, Age Group: young, middle-aged, and old). Of particular interest here is the interaction between the age group and the measurement time point, which will provide insight into the different trajectories within the specific age groups. Thus, power estimation was conducted exemplarily for repeated-measures analyses of variance (ANOVA) of within-between interactions. The sample size was determined based on a small effect size of *f*=0.1 for the mixed ANOVA model with repeated measures (4 time points) and interactions with the Age Group factor (3 categories), given an error probability of α=.05 and a power of 0.95, resulting in a sample size of 264 individuals (determined with G*Power, a free-source statistical software package) [44]. However, having a larger number of subjects is desirable owing to expected dropouts over the long duration of the study. Therefore, a group size of approximately 600 was targeted, as we assumed a dropout rate of up to 20% per time point of the follow-up measures. Assuming this dropout rate, the number of remaining participants 20 years later would be approximately 300, which roughly corresponds to the estimated sample size, as summarized in Table 1.

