### Telephone Interview

Once the participants register via a contact form, they receive a telephone call where an interview is conducted to check their inclusion criteria and obtain personal data, such as age, contact information, education, current occupation (type, full time/part-time), planned changes in the next years (relocation, retirement), pre-existing and current illnesses, physical restrictions, medication, willingness to visit the Leibniz Research Centre for Working Environment and Human Factors at the Technical University of Dortmund (IfADo) for tests on 2 independent days, and the willingness to participate in follow-up tests in 5, 10, and 15 years.

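### A stated reason for leaving cannot show that refusals and relocations are random, yet complete-case ANOVA and unweighted GEE lean on that assumption

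*Protocol article*

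**What the plan says.** All references are to the protocol article.

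- **Limitations and Future Challenges** says that "it is important to analyze the reasons for dropouts and whether the participants are missing at random or not at random", and explains the two terms as unsystematic versus systematic reasons. It then gives examples. On one side, "dropouts due to lack of interest in further participation in the study or change of residence can be treated as random". On the other, "dropouts due to illness or death could reflect a systematic reason for missing data", because older participants carry more risk. The pandemic is also called systematic.
- **Data Analysis** plans mixed ANOVA and ANCOVA for the longitudinal data without imputation. Complete cases are used when few or a moderate number of values are missing, and GEE or MER when more are missing. The choice depends on the amount of missing data, not on the reason.
- **Limitations** later names GEE as the model for this design and MER as an alternative, which it rates as more robust to missing data.
- **Study Population** sets the expected loss: "we assumed a dropout rate of up to 20% per time point of the follow-up measures". Table 1 gives 600, 480, 384 and 307 participants at T1 to T4. Losses are not split by reason.

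**The concern.** Whether a dropout is ignorable depends on how leaving relates to the outcome, given what the model conditions on. The answer on the exit form does not settle it. A refusal is harmless only if those who refuse would have followed the same course as comparable people who stayed.

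The article itself gives grounds for doubt. Hypothesis 1 says that with depression and subclinical depressive symptoms "the sensitivity to rewards is decreased", and expects worse executive performance with high burnout scores. The same symptoms could plausibly reduce willingness to return for two days of testing and also go with worse cognition. Hypothesis 4 concerns work ability and early retirement, and the telephone interview asks in one item about "planned changes in the next years (relocation, retirement", so moving house may follow a change in work status. That second link is the weaker one.

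If the label is accepted without a check, results from returners may be read as describing the enrolled cohort. Decline, and any loss of performance linked to burnout or depression, could then be understated.

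**Working it through.** **1. The plan's own figures.** Retention at 20% loss per wave: 600 × 0.8 = 480; 480 × 0.8 = 384; 384 × 0.8 = 307. Table 1 reproduces. Losses per wave are 120, 96 and 77, in total 293, and 293/600 = 0.488. The required sample also reproduces: for f = 0.1, 3 groups and 4 time points, N = 264 gives power 0.951 (assuming correlation 0.5 between waves and sphericity, which the article does not state). No sample-size figure is in dispute here.

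**2. What each planned method needs.**

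| Method | Condition for an unbiased result |
|---|---|
| Complete-case ANOVA/ANCOVA | generally, missing completely at random |
| Unweighted GEE | generally, missing completely at random |
| MER (likelihood-based) | dropout depends only on observed data in the model |

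The article's contrast of random with not at random passes over the difference between the first two rows and the third. If refusal depends on a measured symptom score, MER including that score can remain valid, while the other two generally do not.

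**3. Possible size among T4 completers.** Let q be the fraction lost, s the share of losses that are refusals or moves, and e their extra decline. With all other losses declining like the returners, the cohort mean exceeds the returners' mean decline by q × s × e. Only q comes from the article; s = 0.5 to 0.8, e = 0.2 to 0.4 SD and the direction are assumed.

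- Low: 0.488 × 0.5 × 0.2 = 0.05 SD
- High: 0.488 × 0.8 × 0.4 = 0.16 SD

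**4. A second illustration with different assumptions.** In a simulation, refusal over three waves depended on baseline depression (odds ratio 1.3 to 2.0 per SD), depression correlated 0.1 to 0.5 in size with change, mean change was -0.30 SD with SD 0.5, and refusals were 50% or 100% of dropout. About 51% were retained. Completers were 0.08 to 0.37 SD less depressed than the enrolled sample. Their mean change was about -0.295 to -0.21 SD, an understatement of roughly 1% to 30%.

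**5. Who is still represented under GEE or MER.** The 96 + 77 = 173 people lost after T2 or T3 contribute at least one follow-up under these models. Only the 120 lost before T2 contribute none. Step 3 therefore overstates the error for those analyses.

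**The case against.** The strongest reply is that the sentence is an illustration in the Discussion and drives no analysis step. It begins as an example, says only that such dropouts can be so treated, and follows a call to analyze the reasons. Data Analysis picks the method by the amount of missing data. With up to 49% lost, that points to GEE or MER, and detailed methods are left to later publications. Much of this stands:

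- A reader might infer an operative rule, under which a wave lost mainly to refusals would be declared random and its results presented as unbiased. The article does not say that.
- A reader might also infer that refusal is known to be tied to depression, exhaustion or work variables. Nothing in the article shows it. Hypothesis 1 speaks of reward sensitivity, not of study participation. Severe depression is excluded and the mean Beck score is 5.7 (SD 6.4). The link is plausible, no more.
- It is tempting to set 0.05-0.16 SD against "a small effect size of *f*=0.1" read as a 0.2 SD difference between two groups. That reading is wrong for a 3 × 4 interaction. With equal groups and one group diverging linearly by D at T4, the interaction SD over the cells is √(2/9) × √(5/36) × D = 0.176 D, so f = 0.1 means D of about 0.57 SD. The error in step 3 also concerns overall mean decline, and in the Age Group by Time interaction it would cancel if refusal were equally selective at all ages.
- Baseline data on dropouts are not complete: for example, the verbal learning score has n = 525, the genotype table N = 528, and hair is sampled only where possible.

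What the reply does not remove is the statement itself. It answers in advance, for two classes of dropout, the question that the sentence before it says must be examined. It does so in a plan whose first-line methods are the ones most exposed if the answer is wrong.

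**Conclusion.** The point holds in a limited form. The article is wrong to offer the stated reason as a basis for treating refusals and relocations as random. The exposure is greatest for complete-case ANOVA and unweighted GEE, and smaller for MER if the predictors of dropout are in the model. Under the assumptions in step 3, T4 completers understate mean decline by about 0.05-0.16 SD, and by less under GEE or MER. These figures illustrate what is possible and do not estimate a bias: the share, the extra decline and its direction are all assumed, and only the 49% cumulative loss comes from the plan. The documents do not support a claim that the error matches the effect on which the study was sized.

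**What to change.** 1. Remove the statement that dropouts from lack of interest or relocation can be treated as random. Keep the intention to record and analyze reasons.
2. At each wave, compare returners with each dropout class (refused, moved, ill, dead) on the available previous-wave cognition, Beck score, burnout scales, Work Ability Index, education, employment and age.
3. Make MER, or inverse-probability-weighted GEE, the main longitudinal analysis in place of complete-case ANOVA or unweighted GEE, and bring in the variables found to predict dropout.
4. Report a not-at-random sensitivity analysis in which refusers' later scores are worse than predicted over a stated range, for example up to the 0.4 SD assumed above.

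The comparisons in item 2 use measures already in the protocol, so the cost is revised analysis wording, a table per wave and modest extra modelling. The downside is a sensitivity range that may look less favourable than a single estimate.

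### GEE is made the lead longitudinal model, with a complete-case branch beside it, for reasons that do not address the systematic dropout the article itself foresees; mixed effect regression on all visits should be primary

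*Protocol article*

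**What the plan says.** Study Population sets the planned loss: "a group size of approximately 600 was targeted" because "we assumed a dropout rate of up to 20% per time point of the follow-up measures". Table 1 turns this into 600, 480, 384 and 307 participants at T1 to T4. The same section singles out the interaction of age group with measurement time as the effect of particular interest.

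Data Analysis gives the rule for longitudinal data: mixed-model ANOVA or ANCOVA without imputation. "In case of a few or moderate number of missing data, the analyses will be conducted with the complete cases". With more missing data, GEE or MER is to be used. The boundary between the two branches is not defined.

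Limitations and Future Challenges discusses why people leave. It gives an example of the harmless kind: "dropouts due to lack of interest in further participation in the study or change of residence can be treated as random". The article sets two other causes against this one: "In contrast, dropouts due to illness or death could reflect a systematic reason for missing data". It adds that loss may be higher among the elderly, and it calls a pandemic a systematic source. It then says "For the present design, a GEE [109] model will be used" and supports this with three properties: robustness to a wrong correlation structure, tolerance of irregular timing, and no need to exclude incomplete participants. MER is presented as the alternative, although the article says it "is even more robust to missing data than the GEE".

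**The concern.** None of the three properties bears on dropout that is related to the outcome. The first is weakened by it. GEE is robust to a wrong working correlation when data are complete or missing completely at random. When dropout depends on earlier scores, the GEE estimate depends on which working correlation was chosen. A likelihood-based mixed model on all visits stays valid in that case if its mean and covariance are well specified. The article thus leads with the model it rates as less robust to its main threat.

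The complete-case branch adds a second problem. Its trigger is undefined, so the choice between ANOVA, GEE and MER can be made after the data are seen. It also discards visits already collected.

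What is at stake is the age-group-by-time effect. If lower scorers leave more often and the old leave most, decline in the old group is understated.

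**Working it through.** **1. Planned loss (Study Population, Table 1).** 600 × 0.8³ = 307.2, which reproduces the stated 307. Loss by T4 is 1 − 0.8³ = 48.8%. This is the maximum, since 20% is given as an upper limit.

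**2. Is this a power problem?** The stated N of 264 (f = 0.1, 3 groups, 4 time points, α = 0.05, power 0.95) is reproduced with a noncentral F, df1 = 6, df2 = 3(N − 3), λ = f²·N·4/(1 − ρ), if ρ = 0.5 and no sphericity correction are assumed. The article gives neither value. Power at 264 is then 0.951, and with 307 complete participants it is 0.977. On these assumptions power is kept; the question is bias.

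**3. Data used by complete cases.** Planned visits are 600 + 480 + 384 + 307 = 1,771. Complete-case visits are 4 × 307 = 1,228, and 1,228/1,771 = 69%.

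**4. Simulation, dropout driven by the last observed score.** Everything in this step is assumed, not taken from the article:
- 200,000 people per age group; random-intercept variance 0.6, slope SD 0.15 per wave, residual variance 0.4.
- Dropout per wave 15/18/30% (young/middle/old). T4 retention is 0.85³ = 61%, 0.82³ = 55% and 0.70³ = 34%. The mean over equal groups is 50%, close to the 51% in Table 1.
- Log-odds of dropout rise by 0.5 to 0.8 per SD lower last score.
- True change over 15 years is -0.75 SD in the old group and 0 in the young group.
- Mean model saturated in time within each group. MER is represented by weighting with the true random-intercept-and-slope covariance, so its result is a best case.

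| Method | Old-group change (truth -0.75) |
|---|---|
| GEE, independence | -0.47 to -0.35 |
| GEE, exchangeable | -0.73 to -0.72 |
| MER | -0.75 |
| Complete cases | about -0.78 |

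The shortfall for independence GEE is (0.75 − 0.47)/0.75 = 37% to (0.75 − 0.35)/0.75 = 53%. For exchangeable GEE it is 3 to 4%.

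For the contrast of interest, independence GEE gives an old-minus-young difference of about -0.62 to -0.56 against -0.75, a shortfall of 17 to 25%. Part of the bias cancels because the young group is biased upward too, by about 0.15 to 0.21 SD (0.62 − 0.47 and 0.56 − 0.35).

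Complete-case change is nearly right here, but the old participants analysed start 0.30 to 0.44 SD above the true baseline mean of their group.

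**5. Same simulation, dropout driven by the current, unseen score.** MER gives about -0.58 to -0.51, so it is 23 to 32% too small. A separate simulation with a true slope of -0.20 per wave, 20% dropout per wave and log-odds of 1 per SD agrees. With dropout driven by the unseen score, MER gives -0.12, exchangeable GEE -0.13 and complete cases -0.16. With dropout driven by the person's own slope, MER gives -0.15, GEE -0.14 to -0.15 and complete cases -0.13. No standard method is safe in these two cases.

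**The case against.** Several stronger readings are tempting, and the article does not support them.

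- **The plan offers only complete cases or an unweighted GEE.** MER is named in both sections. Weights are not mentioned either way. Data Analysis defers detailed methods to later publications, and an article may leave weights and working correlation to a fuller plan. That silence is no finding.
- **The plan relies on an assumption it rejects.** The text on illness, death and the elderly is conditional, and it asks for the reasons for dropout to be examined. It never says that dropout depends on earlier scores. Dropout that differs only by age group does not bias GEE when age group is in the model, as planned. Dependence on scores within an age group is plausible, but it is assumed here.
- **Lack of interest will be analysed as random.** That sentence is an example in the discussion, not an analysis rule. It remains an untested assumption, since people in decline may also lose interest.
- **The two sections contradict each other.** The GEE statement can be read as the second branch of the Data Analysis rule. If so, complete cases would not be used at T4. Loss by T2 is at most 20%, so they might well be used for the first follow-up.
- **Trajectories will be wrong by about half.** That needs an independence working correlation, which the article does not specify. With exchangeable correlation the error is small.
- **Switching to MER solves the problem.** Step 5 shows that it does not when dropout depends on unseen decline.

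These objections limit the size and tone of the point. They do not supply a reason for leading with GEE over MER, nor a definition of the complete-case trigger.

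**Conclusion.** The point holds, at moderate severity. The article recognises possible systematic dropout and plans for up to 49% loss, yet it leads with GEE on grounds that do not address that dropout, ranks MER as more robust but second, and keeps a complete-case branch with an undefined trigger.

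The cost depends on choices not yet stated. With dropout driven by observed scores it runs from a few percent of old-group decline (exchangeable GEE) to more than a third (independence GEE). The rates and strength of dependence behind these figures are assumptions. Severity stays moderate because MER is already an option, a sensible working correlation would remove most of the GEE error in that setting, and the first longitudinal publications were still ahead when the article was written.

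**What to change.** In Data Analysis and in Limitations and Future Challenges:

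1. Name likelihood-based MER, with random intercept and slope and every available visit of every participant, as the primary longitudinal analysis.
2. Replace the complete-case branch and its undefined trigger with that model.
3. Keep GEE as a secondary analysis with inverse-probability-of-dropout weights, built for example from prior cognition, age, education and health, and state the working correlation.
4. Add one not-at-random sensitivity analysis that covers illness and death, such as a pattern-mixture shift or a joint model with death.
5. Present the sentence on lack of interest and moving as an assumption to be checked.

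This needs no new data. The cost is a change of wording, some extra programming, and model-based output in place of simple ANOVA tables.
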